### Improvement of clinical and biological parameters

Time to CRP improvement (< 10 mg/l)

Time to lymphopenia improvement (> 1000/mm3)

Change and percentage change in neutrophil-lymphocyte ratio (NLR) at each visit through day 29

### Days of oxygenation

Oxygen days will be defined as the number of days where patients have any oxygen therapy during hospitalization.

The total number of days will be the sum of all reported days, regardless of whether the days occur consecutively or in disjoint intervals.

Oxygen free days will be analyzed over 28 days. 28- Number of days under oxygen. Death will be imputed to 0 day.

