^1^: Clinical examination: Full physical examination at Day1 and brief targeted examination at other visits. Vital signs: Blood pressure, pulse rate, body temperature, Height (cm) and body weight (kg) (only at D1),.

^2^.Respiratory status: respiratory rate, oxygen supplementation, SpO2 at rest or PaO2, radiographic findings (if available). For outpatients, only supplement oxygenation will be enquired.

^3^: For viral load assessment. Not to be done if screening RT-PCR was obtained in the same study site. After qualitative analysis, nasopharyngeal swab samples to be stored at the site)

^4^: ECG: to be performed at the discretion of the Investigator, as deemed necessary for appropriate patient care

^5^: Serology: HIV, hepatitis B/C, COVID-19 (after analysis remaining serum will be stored under usual conditions at local site)

^6^: Blood analysis: **Hematology**: hemoglobin, hematocrit, red blood cell (RBC) count, white blood cell (WBC) count with differential (absolute counts and including calculation of total lymphocytes), and platelet (PLT) count.

**Serum Chemistry:** creatinine, glucose, total protein, total bilirubin, alkaline phosphatase (ALP), aspartate aminotransferase (AST), alanine aminotransferase (ALT), gamma glutamyltransferase (GGT), C-reactive protein, ferritin,

^7^: Only for patients participating in the ancillary studies

^8^: Immediately before administration and at the end of infusion

^9:^ done only if before day 15

^10^: assessed daily

^11^: For viral load assessment. After qualitative analysis, nasopharyngeal swab samples to be stored at the site)

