## Sample size calculation

In the phase 2b, about 398 randomized patients, 199 patients in each group, will be included.

Assuming a true treatment difference in clinical failure rate of 10% for XAV-19 added to SoC therapy compared to placebo added to SoC therapy where a rate of 20% is expected, a sample size of 398 participants provides at least 80% power that the primary analysis will be statistically significant at the two-sided 5% significance level.

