### Days of Non-invasive ventilation/high-flow oxygen

The median days of non invasive ventilation or high-flow oxygen use during study will be summarized by treatment group. Patients who did not receive non invasive ventilation will have a number of days equal to 0.

Time to non-invasive ventilation/high flow oxygen use will be compared between groups using Fine & Gray method to take into account competing risk (death).

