### Days of invasive ventilation /ECMO

The median days of invasive ventilation or ECMO use during study will be summarized by treatment group.

Time to invasive ventilation/ECMO will be compared between groups using Fine & Gray method to take into account competing risk (death).

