### Days of Oxygen

If the subject’s 8 point ordinal scale is 4, 5, 6, or 7 at the last observed assessment, then the subject will be considered to be on oxygen through Day 29. The endpoint will be total days when assessments are available plus all imputed days following the last observed assessment.

If the subject is not on oxygen at the last observed assessment, then the subject will be considered to not be on oxygen for the remainder of follow-up. Thus, no additional imputed days will be added to the number of days recorded on available assessments.

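### The SAP's exploratory day-counts omit home oxygen, do not place death strictly worst for oxygen-free days and have no death rule for ventilation days; the NIV/high-flow median will be 0 in both arms at the planned rates

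*Combined protocol and SAP*

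**What the plan says.** **Oxygen.** SAP 5.1 (Days of oxygenation) defines oxygen days as "the number of days where patients have any oxygen therapy during hospitalization". It then defines a score: "Oxygen free days will be analyzed over 28 days. 28- Number of days under oxygen. Death will be imputed to 0 day". No floor or cap is given. The endpoint list in SAP 1.3 gives the window as 29 days. Under SAP 5.4 (Days of Oxygen), if the last score is 4 to 7, "then the subject will be considered to be on oxygen through Day 29". Footnote 2 to the phase 2b schedule (protocol 6.2) says: "For outpatients, only supplement oxygenation will be enquired".

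**NIV/high-flow and invasive ventilation/ECMO.** SAP 5.1 sums the reported days, tied to score 5 for NIV/high-flow and to score 6 or 7 for ventilation/ECMO. SAP 5.4 carries days forward to Day 29 only if the last score is 5, or 6 to 7, respectively. Neither section mentions death. For hospital days, by contrast, SAP 5.4 sets an in-hospital death to 28 days.

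**Summaries.** SAP 5.2 reports medians by arm. For NIV/high-flow: "Patients who did not receive non invasive ventilation will have a number of days equal to 0". For invasive support: "The median days of invasive ventilation or ECMO use during study will be summarized by treatment group", with no rule for non-users. SAP 5.2 plans no analysis of oxygen-free days; its oxygen paragraph covers time to weaning only.

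**The concern.** Duration of each support is a stated secondary objective (SAP 1.2, items d to f). A duration is useful only if a worse course gives a worse value, and the rules break that in three places.

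- Earlier discharge on oxygen is credited as less oxygen.
- A death can score the same as, or better than, a survivor who stayed on oxygen.
- A patient who dies soon after intubation has a shorter ventilation time than one who is ventilated longer and recovers.

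An arm with more early deaths, or more discharges on oxygen, could look better on these measures. Separately, a median over all patients says nothing when most of them never receive the support.

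**Working it through.** **Planned rates.** SAP 2.7 assumes 20% failure on placebo and a difference of 10%, and says "a sample size of 398 participants provides at least 80% power" for a result that is "statistically significant at the two-sided 5% significance level". Taking the difference as absolute (20% vs 10%, pooled rate 0.15, pooled variance, no continuity correction):

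n = [1.960 × √(2 × 0.15 × 0.85) + 0.842 × √(0.20 × 0.80 + 0.10 × 0.90)]² / 0.10² = 199 per arm, 398 in total, with power 0.8001. The plan's figure is reproduced, so 20% and 10% are its Day 15 planning rates.

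**Home oxygen.** Take a patient discharged on D4 who uses oxygen at home to D29.
- SAP count: D1-D4 = 4 days, so the score is 28 - 4 = 24.
- Days not counted: D5-D29 = 25.
- This is a worst case for one patient. The documents give no frequency of home oxygen.

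**Oxygen-free days.** D1 to D29 inclusive is 29 days.

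| Patient | Oxygen days | Score |
|---|---|---|
| Survivor, 27 days | 27 | 1 |
| Survivor, 28 days (or capped at 28) | 28 | 0 |
| Survivor, D1-D29, no cap | 29 | -1 |
| Death | any | 0 |

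Death is not strictly worst under either reading.

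**Death and ventilation days.** SAP 5.1 links its composite of respiratory failure or death to scores 5 to 8, and SAP 5.4 calls 7 the highest score for a hospitalized subject. Death is therefore taken as score 8, which does not trigger carry-forward.
- Ventilated D3, dead D4: 1 or 2 days, depending on how the day of death is scored.
- Ventilated D3-D12, survived: 10 days.
- Ventilated from D3, lost to follow-up on D4: carried D3-D29 = 27 days.

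As an illustration with assumed values, let 10% of an arm be ventilated, survivors average 13 ventilated days, and half of the ventilated die. If the deaths come after 2 ventilated days, the all-patient mean is 0.10 × (13 + 2)/2 = 0.75 days. If they come after 5, it is 0.10 × (13 + 5)/2 = 0.90 days. Earlier death gives the better figure.

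**Median.** With 199 per arm the median is the 100th ordered value, so it exceeds 0 only if at least 100 patients have one or more support days. P(Binomial(199, p) ≥ 100):

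| Share ever supported, p | P(median > 0) |
|---|---|
| 10% | 1.5 × 10⁻⁴⁶ |
| 20% | 1.9 × 10⁻²¹ |
| 30% | 1.8 × 10⁻⁹ |
| 40% | 0.002 |
| 45% | 0.08 |
| 50% | 0.50 |

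The planned 10% and 20% also include death and reservoir-mask oxygen, so the share with NIV/high-flow or ventilation by Day 15 would be lower still. Day 29 shares are not given; rates above 20% are assumptions shown as a range. These endpoints use the mITT population, so n may fall slightly below 199, but about half the arm must still be supported.

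**The case against.** The strongest reply is that death is already handled where arms are compared. SAP 5.2 compares time to weaning, to NIV/high-flow and to invasive ventilation/ECMO by Fine & Gray with death as a competing risk. Mortality is analysed separately, and death is part of the primary composite. That stands, and it limits the defect to the duration measures. It does not repair them, because time to first use is not duration.

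Second, a median of 0 in both arms cannot also favour the arm with more deaths. That is right for any one summary. The two faults belong to different summaries: the all-patient median is uninformative, while the missing death rule affects means and the linear mixed model that protocol 7.2.1 plans for quantitative endpoints.

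Third, the carry-forward rules sit under Missing Data, and no text says that a death is processed as not on support. This is also true. The firm statement is that no death rule exists for these two durations and that a plain sum of days stops at death.

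Fourth, time to weaning and the proportion without oxygen at D8, D15 and D29 are not restricted to hospital oxygen. They partly cover the home-oxygen gap, but not in the day count.

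A reader might also infer more than the documents support:
- That median oxygen days will be 0. Every patient needs oxygen at screening, so it will not be.
- That survivors rank materially below death. The gap is one day, depends on counting D1-D29, and no rank analysis of oxygen-free days is planned.
- That at most 20% can receive support. That figure is a Day 15 planning rate, not a cap to Day 29.
- That no treatment effect on support could be shown. Incidence, time-to-event analyses and the protocol's means remain.

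**Conclusion.** The point holds for three definitions: oxygen days that stop at discharge, an oxygen-free score that does not place death strictly worst, and NIV/high-flow and ventilation days without a death rule. The sizes are up to 25 days for one patient in the D4-discharge example, one day (-1 vs 0) or a tie for the oxygen score, and 1 or 2 days against 10 in the ventilation example.

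The NIV/high-flow median will be 0 in both arms at the planned rates, and very probably even if 40% of an arm were supported. For invasive ventilation/ECMO this follows only if non-users are counted as 0, which SAP 5.2 does not say.

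The conclusions rest on D1-D29 counting as 29 days unless capped, and on death being score 8. SAP 3.1 treats all secondary objectives as exploratory, and the primary analysis is unaffected. The changes are still worth making, because the rules as written give misleading values and SAP 3.1 relies on effect sizes with CIs, which the planned medians do not provide.

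**What to change.** Before unblinding, amend SAP 5.1, 5.2 and 5.4 as follows.

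1. Use one 28-day window for oxygen, NIV/high-flow and invasive ventilation/ECMO, with the first and last day stated (for example D2-D29), and end the carry-forward rules on the same day.
2. Define support-free days for each support. Bound survivors at 0-28 and place death by the end of the window strictly below 0, for example at -1.
3. Count oxygen after discharge, using the scheduled outpatient contacts.
4. In place of the all-patient median of NIV/high-flow and ventilation days, report the number ever supported and a between-arm effect estimate with CI for support-free days, for example from a rank-based or proportional-odds comparison.
5. Keep the planned Fine & Gray time-to-event analyses.

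The cost is SAP wording and derivation code; outpatient oxygen is already asked about. The one real drawback is that home-oxygen days between contacts must be carried between reported dates. For discharged patients outside the ancillary studies the scheduled contacts are D5, D8, D15 and D29, so the longest gap is 29 - 15 = 14 days. The carrying rule should be written down, and a sensitivity analysis could vary it.

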### Days of Non-invasive ventilation/high-flow oxygen

Non-invasive ventilation/high flow-oxygen days should be associated with the ordinal scale equal to 5.

The total number of days will be the sum of all reported days, regardless of whether the days occur consecutively or in disjoint intervals.

### Days of Ventilation/ECMO

Ventilator / ECMO days should be associated with the ordinal scale equal to 6 or 7.

The total number of days will be the sum of all reported days, regardless of whether the days occur consecutively or in disjoint intervals.

### Days of Hospitalization

Duration (in days) of the initial hospitalization will be defined as the number of days from D1 to discharge.

### Death

For analysis of death, the time to death will be defined as the elapsed time (in days) from D1 to death.

## Analysis methods

### Baseline characteristics

Detail of baseline characteristics are reported in table 1. Baseline characteristics will be described, in overall and according treatment groups. Quantitative variables will be expressed as mean (standard deviation) or median (interquartile range) for non-Gaussian distribution. Categorical variables will be expressed as frequencies and percentages. The number of missing data will be also reported. No formal statistical comparisons will be done; clinical importance of any imbalance will be noted.

### Primary and key secondary outcome analyses

Proportion of patients who die, develop respiratory failure (requiring noninvasive ventilation, high-flow oxygen devices or invasive mechanical ventilation) between Day 1 and Day 15 (Day 8 and Day 29) will be compared using a logistic mixed model to take into account stratification factors: duration of symptoms prior to screening (fixed effect) and center (random effect).

In cases of convergence failure, sensitivity analysis of the primary outcome will be performed to assess the impact of individual centers on the observed treatment effect. If centers effect is not relevant, final model will not include the center.

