### Primary endpoint

Patients who died or develop respiratory failure, as defined by the requirement of noninvasive ventilation, high-flow oxygen devices, invasive mechanical ventilation (corresponding to a score of 5 or more on the WHO 8 point ordinal scale) or by an increase of the required O2 supplement more or equals to 10 L/minutes with a non-rebreather mask (oxygen mask with reservoir bag).

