### Secondary endpoint(s)

**The key secondary endpoints are the**:

Proportion of patients who die, develop respiratory failure, as defined by the requirement of noninvasive ventilation, high-flow oxygen devices or invasive mechanical ventilation at Day 8 and Day 29.

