Proportion of patients who die, develop respiratory failure (requiring non-invasive ventilation, high-flow oxygen devices or invasive mechanical ventilation) between baseline and Day 15 will be compared using a logistic mixed model to take into account stratification factors (duration of symptoms prior to enrolment and sites).

Secondary hypotheses have been ordered according to relative importance.

The key secondary outcome, which is the proportion of patients who die, develop respiratory failure (requiring non-invasive ventilation, high-flow oxygen devices or invasive mechanical ventilation) between baseline and Day 8 and Day29 will be analysed as the primary endpoint.

Others secondary endpoint :

Quantitative endpoint will be compared using linear mixed model and qualitative data with logistic mixed model to take into account stratification factors.

Time data’s will be analyzed using survival model (Kaplan-Meier, Cox model). Fine & Gray method will be used to take into account competing risk.

Safety Analyses

The safety population is defined as all subjects randomized into the study but excluded who are ineligible at baseline or who have not had any dose of treatment.

Safety endpoints include death through Day 29 and through Day 60, SAEs and Grade 3 and 4 AEs. These events will be analyzed univariately. Time-to-event methods will be used for death. Each AE will be counted once for a given subject and graded by severity and relationship to COVID-19 or study intervention. AEs will be coded using the current version of the Medical Dictionary for Regulatory Activities (MedDRA). AEs will be presented by system organ class, duration (in days), start- and stop-date. Adverse events leading to premature discontinuation from the study intervention and serious treatment-emergent AEs will be presented either in a table or a listing.

More details will be described in the Statistical Analysis Plan.

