## Endpoints

### Primary criterion

Patients who died or develop respiratory failure, as defined by the requirement of noninvasive ventilation, high-flow oxygen devices, invasive mechanical ventilation (corresponding to a score of 5 or more on the WHO 8 point ordinal scale*), or patients with low oxygen delivery device and a flow ≥ 10 L / min with reservoir.

Efficacy will be evaluated between baseline (D1 before infusion) and Day 15.

*Cf §5.1.2

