### Clinical status: WHO 8 point ordinal scale

The ordinal scale of the clinical status will be assessed at each study visit.

Each day, the worse score of the day will be recorded.

Reference: <https://www.who.int/blueprint/priority-diseases/key-action/COVID-19_Treatment_Trial_Design_Master_Protocol_synopsis_Final_18022020.pdf>

[figure not shown]

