### Respiratory failure or death

Respiratory failure is defined by a requirement of low oxygen delivery device and a flow ≥ 10 L / min with reservoir, or high-flow oxygen devices or noninvasive ventilation, or invasive mechanical ventilation or death after infusion of treatment. This is related to a value of 5, 6, 7, or 8 on the clinical status 8-point ordinal scale.

Respiratory failure will be evaluated between baseline and day 15 (primary objective), between baseline and day 8, and between baseline and day 29 (key secondary objectives).

The primary outcome measures the number of patients who had at least one respiratory failure after baseline (D1 before infusion).

The time to respiratory failure will be defined as the elapsed time (in days) from baseline (on Day 1) to the first day at which a subject reaches any respiratory failure.

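### Reservoir-mask oxygen at 10 L/min or more is respiratory failure in the endpoint definitions but absent from the analysis text, and the plan does not settle which version will be analysed

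*Combined protocol and SAP*

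**What the plan says.** **With the reservoir component.** The protocol's Phase 2b primary endpoint (section 3, Primary endpoint) lists death, non-invasive ventilation, high-flow oxygen and invasive ventilation, then adds "or by an increase of the required O2 supplement more or equals to 10 L/minutes with a non-rebreather mask". SAP 1.3 (Primary criterion) adds "or patients with low oxygen delivery device and a flow ≥ 10 L / min with reservoir", and the SAP key secondary criteria do the same for Day 8 and Day 29. SAP 5.1 (Respiratory failure or death) opens with it: "Respiratory failure is defined by a requirement of low oxygen delivery device and a flow ≥ 10 L / min with reservoir".

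**Without it.** SAP 5.2 (Primary and key secondary outcome analyses) states the comparison as "Proportion of patients who die, develop respiratory failure (requiring noninvasive ventilation, high-flow oxygen devices or invasive mechanical ventilation) between Day 1 and Day 15", and the same sentence covers Day 8 and Day 29. Protocol 7.2.1 has "respiratory failure (requiring non-invasive ventilation, high-flow oxygen devices or invasive mechanical ventilation) between baseline and Day 15 will be compared". The protocol's key secondary endpoint is also without it: "as defined by the requirement of noninvasive ventilation, high-flow oxygen devices or invasive mechanical ventilation at Day 8 and Day 29".

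**The link to the ordinal scale.** After a definition that includes the reservoir mask, SAP 5.1 says: "This is related to a value of 5, 6, 7, or 8 on the clinical status 8-point ordinal scale". SAP 5.2 (8-point ordinal scale over 29 days) analyses time to respiratory failure from scores 5 to 8 alone.

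**Data collection.** The Phase 2b schedule places oxygen supplementation under respiratory status at screening and on D1, D2, D3, D5, D8, D15 and D29. The protocol has the ordinal score recorded daily to Day 29. SAP 5.1 says "The ordinal scale of the clinical status will be assessed at each study visit", but its next sentence refers to each day's worst score.

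**The concern.** SAP 3.1 treats all secondary objectives as exploratory, so the primary endpoint carries the trial's only confirmatory test. A programmer who follows SAP 1.3 and the opening of SAP 5.1 will count a patient whose worst state was a reservoir mask at 10 L/min or more. A programmer who follows SAP 5.2, protocol 7.2.1 or the score 5 to 8 rule will not. The two event sets can differ in both arms.

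The definition also affects the per-protocol population, because SAP 3.2 makes respiratory failure before treatment a major deviation. If the conflict is still open when the Day 29 data are unblinded (protocol 4.3.3, SAP 2.6), choosing a version afterwards would be open to the charge that the results guided it.

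**Working it through.** **1. Where a reservoir-mask patient falls on the scale.** The figure of the 8-point scale is not shown, so this is inferred from the text.

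- SAP 5.1 (Days of Non-invasive ventilation/high-flow oxygen) ties those days to score 5.
- SAP 5.1 (Days of Ventilation/ECMO) ties those days to scores 6 and 7.
- SAP 5.4 (Days of Oxygen) treats scores 4, 5, 6 and 7 as being on oxygen, so 4 is the only on-oxygen score left.
- SAP 1.3 attaches the phrase about a score of 5 or more to the ventilation and high-flow items, then adds the reservoir mask with a separate *or*.

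On these sections the patient scores below 5, and a rule that uses only scores 5 to 8 misses the event. SAP 5.4 (Primary and key secondary outcome) fills gaps with an ordinal score of 7 or 2, which points towards a score-based derivation.

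**2. Coverage of days.** The endpoint is at least one failure between baseline and Day 15. D4, D6, D7 and D9 to D14 have no scheduled record of flow or device.

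**3. The planned sample size.** Inputs from SAP 2.7 and 2.4: 20% versus 10%, two-sided 5%, 80% power, 1:1. With pooled variance and no continuity correction:

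n per arm = [z(0.975)·√(2p̄(1−p̄)) + z(0.80)·√(p1(1−p1)+p2(1−p2))]² / (p1−p2)²

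= [1.960·√(2·0.15·0.85) + 0.842·√(0.16+0.09)]² / 0.10² = 199 after rounding up, or 398 in total. Power at 199 per arm is 80.0%, so the stated figure reproduces exactly.

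**4. Sensitivity to the definition.** The documents give neither the share of failures that are reservoir-only nor the definition behind the 20%; both sample-size sections speak only of a clinical failure rate. The shares and added points below are therefore assumptions. Power is for 199 per arm, by the same method.

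*(a) 20% versus 10% is the full definition, and reservoir-only events are dropped:*

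| Assumed reservoir-only share | Rates analysed | Power |
|---|---|---|
| 10% | 18% vs 9% | 75.0% |
| 20% | 16% vs 8% | 69.1% |
| 30% | 14% vs 7% | 62.5% |

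Expected events are 199·0.20 + 199·0.10 = 59.7, so shares of 10%, 20% and 30% change the status of about 6, 12 and 18 patients.

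*(b) 20% versus 10% is the narrower definition, and the component is added:*

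| Points added to control rate | Power, risk ratio stays 0.5 | Power, added events unaffected by treatment |
|---|---|---|
| 2 | 84.3% (22% vs 11%) | 75.9% (22% vs 12%) |
| 5 | 89.4% (25% vs 12.5%) | 70.5% (25% vs 15%) |
| 8 | 93.2% (28% vs 14%) | 66.0% (28% vs 18%) |

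The definition can move power in either direction.

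**The case against.** The strongest reply is that SAP 5.1 governs. It sits inside the SAP's Statistical methods section, includes the reservoir mask, applies one definition to Day 8, Day 15 and Day 29, and says that the primary outcome counts patients with at least one such failure. The bracket in SAP 5.2 could then be shorthand in a sentence whose purpose is to specify the model, and protocol 7.2.1 defers to the SAP for detail. This stands against the inference that the endpoint to be analysed is known to be the wrong one. It does not remove the conflict, because the score mapping in the same part of SAP 5.1 and the score-only analysis in SAP 5.2 pull the other way.

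The mapping sentence does not simply leave the component out: it follows a definition that contains it, and so claims to cover it. The difficulty is that this claim disagrees with SAP 1.3 and with the SAP's own use of score 5. Because the scale figure is not shown, the inference is reasonable but not certain.

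A reader might also infer that reservoir-mask episodes between visits are lost. The documents do not show that. The eCRF is not included, days of oxygen therapy are themselves an endpoint, and the protocol's section on data sources places data outside its short list in the medical file. What can be said is that flow and device are not scheduled between visits and that no retrieval is planned.

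Nor do the Day 8, Day 15 and Day 29 endpoints differ within the SAP. That mismatch exists only between the protocol's primary and key secondary endpoints.

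**Conclusion.** The point holds as an unresolved contradiction on the primary endpoint. The reservoir component is in four definition sections, missing from both descriptions of the primary comparison and from the protocol's key secondary endpoint, and probably missed by any derivation from scores 5 to 8. It changes which patients are events, so it must be settled before unblinding.

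The documents do not support the stronger conclusions that the wrong endpoint will be analysed or that the trial is underpowered. The sample size of 398 is arithmetically correct and needs no change on this ground. The power range, from about 63% to 93% across the scenarios shown, rests wholly on assumed shares and effects and is illustrative.

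A smaller matter belongs with it: the protocol's wording about an increase can be read as a rise of 10 L/min, whereas the SAP requires a flow of at least 10. Every patient enters on some oxygen, at most 6 L/min, so the first reading would set a threshold above 10.

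**What to change.** Before the Day 29 unblinding:

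1. Use the SAP 1.3 definition, word for word, in the protocol's Phase 2b primary and key secondary endpoints, protocol 7.2.1, SAP 5.1 and both relevant parts of SAP 5.2, changing only the time window. This also resolves the wording about an increase.
2. Replace the score mapping in SAP 5.1 and the time-to-failure rule in SAP 5.2 by: *score of 5 or more, or a low-flow device with reservoir at 10 L/min or more*.
3. State that this component is derived from recorded device and flow, taken from the chart for days between visits.
4. State which definition the 20% control rate refers to.

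A sensitivity analysis on a score of 5 or more is optional. The cost is wording changes in both documents and retrieval of flow and device for the days between visits, with no extra patients or procedures.

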## Randomization

Enrollment and randomization of subjects is done online, using the eCRF, the day of the infusion or the day before.

Eligible subjects will be randomized and assigned in a 1:1 ratio to either Xav19+Soc or placebo+Soc, with stratification by site and by duration since onset of COVID symptoms (1-6 days, 7-10 days, 11-14 days).

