## Covariates and Subgroups

Subgroup analyses for the main efficacy outcomes will evaluate the treatment effect across the following subgroups:

• Duration of symptoms prior to enrollment

o <= 6 days; 7 to 10 days, 11 to 14 days

• COVID serology at randomization

o Positive

o Negative

• Oxygene Flow at randomization

o < 4l/min

o >=4 l/min

• Immunodepressive status (Solid tumor, leukemia, lymphoma, metastatic solid tumor, HIV)

o Positive

o Negative

• Comorbidities

o Number of conditions : None; One; Two or more

• Clinical status at baseline (NEWS score):

2-4

o 5-6,

o 7 and more

• Concomitant treatment of COVID if possible

• Concomitant treatment of coexisting conditions

• Age

o < 50

o 50-65

o 65-75

o > 75

or by the median (or quartiles) according to the sample size

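### The primary model adjusts only for symptom duration and center; pre-specifying baseline oxygen flow and age could add 0 to about 5 points of power, and the primary effect measure should be named

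*Combined protocol and SAP*

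**What the plan says.** SAP 5.2 (Primary and key secondary outcome analyses) specifies a "logistic mixed model to take into account stratification factors: duration of symptoms prior to screening (fixed effect) and center (random effect". Protocol 7.2.1 names the same two factors. If the model does not converge, the SAP looks at the influence of individual centers and may drop center.

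SAP 5.3 is headed Covariates and Subgroups but lists only subgroups. They include "Oxygene Flow at randomization", cut at 4 L/min, and age, in bands. SAP Table 1 tabulates both variables by arm. Protocol 6.2.1 and 6.2.2 record oxygen supplementation at screening and again on Day 1 before infusion. Protocol 7.2.7 has year of birth entered at randomisation.

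SAP 2.4: "Eligible subjects will be randomized and assigned in a 1:1 ratio", stratified by site and symptom duration only.

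SAP 2.7 sizes the trial thus: "Assuming a true treatment difference in clinical failure rate of 10" percent, against "placebo added to SoC therapy where a rate of 20% is expected", so that "a sample size of 398 participants provides at least 80% power" for a result that is "statistically significant at the two-sided 5% significance level". The SAP does not say whether the primary result will be an odds ratio, a risk ratio or a risk difference. SAP 3.1 speaks only of effect sizes with intervals for the secondary objectives, and SAP 5.2 mentions odds ratios for 28-day mortality.

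**The concern.** The endpoint and baseline oxygen flow lie on one axis. Patients may enter at any flow up to 6 L/min, and one route to failure is reaching 10 L/min or more with a reservoir mask (SAP 1.3 and 5.1). A patient near the entry limit starts closer to that threshold than one at 1 or 2 L/min. Age is a plausible second predictor.

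Randomisation balances neither factor by design, and the model corrects for neither, so a chance imbalance passes into the treatment estimate. SAP 5.2 says that any imbalance will be remarked on but not tested, and gives no rule for handling it. That leaves room for a post hoc adjustment that could be disputed.

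The planned power has no reserve, so a modest gain is worth having.

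A second, separate gap is that the trial is sized on an absolute difference, while the specified model returns a conditional odds ratio and no effect measure is named.

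**Working it through.** **Inputs from the documents.** Control rate 20%; difference 10 points, so 20% versus 10%; two-sided alpha 5%; power at least 80%; "199 patients in each group" (SAP 2.7).

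**Step 1: reproduce the sample size.** Normal approximation with pooled variance, no continuity correction:

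n per arm = [1.960 × √(2 × 0.15 × 0.85) + 0.842 × √(0.20 × 0.80 + 0.10 × 0.90)]² / 0.10² = (0.990 + 0.421)² / 0.01 ≈ 199.

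Total 398, power 80.0%. The stated figure reproduces. It does so only if the 10% is absolute: a relative reading (20% versus 18%) would give about 7% power.

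**Step 2: power with the two covariates.** The documents give no prognostic strength for age or flow, so these odds ratios per SD are assumptions. Each scenario had 3,000 simulated trials of 398 patients, with marginal rates held at 20% and 10%. Logistic regression on treatment and symptom duration was compared with the same model plus age and flow. The two figures in each cell are for a center SD of 0 and 0.3 on the logit scale. Monte Carlo error is about 0.7 points.

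| OR per SD, age / flow | Current covariates | Plus age and flow |
|---|---|---|
| 1.0 / 1.0 | 79.9, 80.0% | 79.9, 80.3% |
| 1.25 / 1.25 | 80.6, 79.5% | 80.8, 80.3% |
| 1.5 / 1.5 | 80.5, 80.1% | 81.3, 81.7% |
| 1.5 / 2.0 | 80.2, 79.4% | 82.9, 82.9% |
| 2.0 / 2.0 | 79.4, 80.2% | 83.9, 85.0% |

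In the last row, dichotomising flow lowers the adjusted power to 82.5% and 84.5%.

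Limits of the simulation: covariates were independent and normal, symptom duration had no prognostic effect, and center was not fitted as a random effect.

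**Step 3: cross-check.** Treat adjustment as raising the effective sample to n/(1 − R²). R² of 2%, 5% and 10% gives 80.8%, 82.0% and 84.0% power at 398 patients, the same range.

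**Step 4: chance imbalance.** The difference in mean flow between arms has standard error √(2/199) ≈ 0.10 SD. An imbalance of 0.2 SD or more therefore arises in about 4 to 5% of trials. With flow at OR 1.5 to 2.0 per SD (assumed), a 0.2 SD imbalance moves the unadjusted risk difference by about 1.0 to 1.4 points, against a 10-point target.

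**Step 5: event count.** Expected Day 15 events: 199 × 0.20 + 199 × 0.10 = 39.8 + 19.9 ≈ 60. The fixed slopes would be treatment, two for duration, age and flow: 60/5 = 12 events per slope. Events accumulate, so Day 8 can have no more than this.

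**Step 6: the risk difference.** A standardised risk difference (each patient's predicted risk under each arm, averaged) came out near −0.10 from both models. In the 2.0 / 2.0 scenario its SD was about 0.035 without age and flow and 0.033 with them. The risk difference is therefore available without the extra covariates, which only sharpen it slightly. The odds ratio behaves differently: the marginal value is (0.10/0.90)/(0.20/0.80) = 0.44, while the conditional value in that scenario is about 0.40.

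**The case against.** The strongest reply is that nothing here is wrong. The sample size and power reproduce, both stratification factors are in the model, and randomisation protects the type I error without further covariates. Baseline flow and age appear by arm in Table 1, so readers would see an imbalance. All of that stands.

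The gain also rests wholly on assumed prognostic strength, and the 6 L/min entry limit narrows the spread of flow. That stands too, and is why the size is given as a range starting at zero.

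The change has small costs. The model already carries a random effect over up to about 40 sites, and the SAP foresees convergence failure. Twelve events per slope leaves little room, and Day 8 may have fewer. Screening flow and Day 1 flow can differ, so baseline has to be defined. One sentence in the SAP settles each of these.

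A reader might infer that a risk difference was planned and that adding covariates would deliver it. The documents support neither: the 10 points are only the sizing assumption, and a logistic model with more covariates still gives a conditional odds ratio.

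**Conclusion.** The point holds as an efficiency and reporting improvement, not as an error. It would be wrong to infer that the trial is underpowered or its primary analysis biased: the plan delivers the power it states under its own assumptions.

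The likely change in power is about 0 to +1 point if flow and age are weak predictors (OR per SD up to 1.25), +1 to +2 if moderate (1.5) and +3 to +5 if strong (one or both at 2.0). If they predict nothing, essentially nothing is lost. A reader might infer a larger gain: one simulation with covariates reaching a c-statistic of 0.79 went from 82% to 88%. The documents give no basis for assuming that strength.

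Protection against chance imbalance is a further benefit. The unnamed primary effect measure is a separate gap and does not depend on whether the covariates are added.

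**What to change.** Amend SAP 5.2 and 5.3 before the Day 29 unblinding described in SAP 2.6:

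1. **Covariates.** Add baseline oxygen flow (L/min, continuous) and age (continuous) as fixed effects in the primary and key secondary models. Define baseline flow as the Day 1 pre-infusion value, in line with SAP 5.1, using the screening value if it is missing. Add no other covariates.
2. **Sensitivity analysis.** Keep the currently specified model for this purpose.
3. **Convergence.** State that flow and age remain in the model if center has to be dropped.
4. **Effect measure, as a separate step.** Name the primary measure. Report a standardised (marginal) risk difference with 95% CI, by delta method or bootstrap, beside the odds ratio, so that the result can be read against the 20% versus 10% on which the trial is sized.

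The cost is about one SAP paragraph and no new data. The downside is that the adjusted odds ratio is not numerically comparable with the less-adjusted one; the marginal risk difference gives readers a common scale.
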